##### The PROSPECT Programme

In addition to TAU, participants randomly allocated to the PROSPECT programme group will also receive access to a targeted psychological therapy for suicidal male prisoners. The PROSPECT programme is a structured, time-limited, manualised psychosocial intervention developed to treat male prisoners experiencing suicidal ideation and behaviour [73, 83]. The focus of the PROSPECT programme is informed by empirical work that has tested a theoretically-informed psychological model of the mechanisms underlying suicidal thoughts and behaviours amongst prisoners [34, 74]. The PROSPECT programme comprises of a preparatory phase, followed by a CBSP phase.

##### Preparatory phase

The preparatory phase focuses upon developing open, warm and enthusiastic communication between the practitioner and participant, a key requirement for the necessary trusting therapeutic relationship. Supplemented by self-help resources, the practitioner will encourage the participant to reflect upon their motivation for engagement in the PROSPECT programme and clearly delineate preferred outcomes following therapy. The practitioner will also support the participant to develop an understanding of their previous experiences of suicide ideation and behaviour and collaboratively formulate key areas for intervention.

##### CBSP phase

According to our Schematic Appraisals Model of Suicide (SAMS; [47]), the CBSP phase directly targets (i) information processing biases, (ii) appraisals, and (iii) a suicide schema, since these are the psychological processes that trigger and maintain suicidal thoughts and behaviour. Additionally, CBSP has demonstrable potential to address the interactions between clients’ imported vulnerabilities and the toxic prison environment that can culminate in suicidal thinking and behaviours. CBSP draws from established clinical techniques to restructure the three aspects of the SAMS model, including the use of techniques to encourage participants to evaluate appraisals of themselves, their situation and their future, as well as the use of behavioural techniques to identify and rehearse more helpful responses to distressing situations.

##### Duration of the PROSPECT Programme

Commencing after randomisation, delivery of the PROSPECT programme consists of up to 20 therapy sessions, delivered across a 6-month therapy window, with each 1:1 therapy session typically lasting 30 to 60 min. As shown in the PROSPECT Therapy Session Planner (see Fig. 2), the initial preparatory phase takes place over the first 6 sessions, with the CBSP phase delivered from session 6 through to session 20. This session planner should only be seen as a guide for the practitioner, with differences expected across patients as delivery is tailored according to individual needs. Nonetheless, specific sessions will be dedicated to the required tasks/techniques within both the preparatory phase and the CBSP phase. For example, within the CBSP phase, up to 5 sessions are assigned to the delivery of each specific therapeutic technique (e.g. appraisal restructuring). This is in accordance with the evidence base for each technique listed. The session planner recognises the opportunity to deliver multiple therapeutic techniques within a given session thus offering a more comprehensive targeting of the psychological architecture behind the patient’s suicidal thinking. However, this approach also presents a limiting factor since an excessive number of techniques being delivered within a single session is likely to undermine the focus of the session, confuse the patient, and so reduce potential for benefit. As such, we have learned to limit the concurrent delivery of therapeutic techniques to no more than 3 techniques within a single session. This delivery format for the PROSPECT programme is consistent with our previous and ongoing trials of psychological therapy to suicidal patients, within inpatient and community settings [33, 36, 83].

**Fig. 2 Fig2:**
[figure not shown]
PROSPECT Programme Session Planner

### Drop-out from trial intervention criteria

Participants can choose to stop receiving the therapy or they can be withdrawn from the therapy by the trial therapists. In the case of the latter, trial therapists will consult with the participant and the prison and healthcare staff about continuation in the intervention if there is any deterioration in suicidal risk that is deemed to be related to participation in the research trial. Specific criteria for consideration of participant withdrawal will be:Occurrence of suicidal behaviour.Hospitalisation due to suicidal crisis.Clinically significant increase in frequency or intensity of suicidal ideation.

Contingency plans for participants fulfilling any of the above criteria are in line with normal good clinical practice and NICE guidelines [64]. However, if either participant preference and/or clinical judgement indicate a need for participant ‘drop-out’ from treatment for alternative interventions, these will be pursued.

We note that some participants allocated to the PROSPECT programme arm may exercise their right to withdraw from the intervention whilst remaining a participant of the trial. The reason for drop-out will be requested and recorded in the eCRF but the participants’ rights to not state a reason will be respected. Individuals who drop-out of the treatment but remain participants within the trial, will be invited to complete the 6-month follow-up assessment. Such participants will be identified as ‘non-completers’ and distinguished from those who complete treatment (‘completers’) with further sensitivity analyses conducted accordingly.

### Elective discontinuation from the trial by individual participants

Discontinuation from the trial can be decided upon by individual participants. As stated in the consent forms, deciding to no longer participate results in no detriment to participants. Reasons for discontinuing in a trial, as decided by participants, are varied. For example, participants may find that they are no longer willing to engage in the research activities (e.g. researcher interviews, therapy sessions) or have other family or work commitments which they would prefer to prioritise attending. The reason for discontinuation will be requested and recorded in the eCRF but the individual’s rights to not state a reason will be respected. The characteristics of the participants who withdraw or are lost to follow-up will be compared with those that remain within the trial and a sensitivity analysis will be conducted to assess the effects of any missing data.

### End of trial

The trial will end after the last patient recruited at baseline has completed the 6 month (window of 5–9 months) follow up. The declaration of end of trial will be submitted to REC within 90 days of its completion. Following this, all sites will be advised on the process for closing the trial at sites.

### Outcome measures

#### Co-primary outcomes

There are two co-primary outcomes for the trial. The first outcome is a measure of suicidal ideation, planning and intent over the last week. This will be assessed using the *Beck Scale for Suicide Ideation* (BSSI: [3]). This self-report questionnaire has been used extensively in clinical samples, including prisoner patients [74, 89]. The second co-primary outcome is the number of occurrences of suicidal behaviour (SB) during the 6 months from randomisation. Instances of suicidal behaviour will be collected via self-report from participants with researchers using an adapted version of the *Suicide Attempt – Self-Injury Interview* (SASI: [52]) to improve recall and reporting of SB. Following the EME guidance for multiplicity issues in clinical trials, these two primary outcomes are ranked in terms of clinical importance – BSSI, followed by SB.

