### Demographic, clinical and criminological data

In addition to the outcome measures detailed above, a range of demographic (age, gender, ethnicity), clinical (mental health diagnoses, previous suicide behaviour) and criminological (index offence, sentence length, previous imprisonments) details will also be collected at baseline. The researcher will also complete a contact sheet for each participant, which will include contact numbers and addresses provided by the participant, as well as a list of services they are likely to be in contact with post-release. This sheet will be completed in collaboration with the participant and the participant will sign the form to confirm they give the research team permission to contact them via the relevant services. Furthermore, clinical and prison records will be accessed, subject to participant consent, to collect relevant information that the participant is unable to self-report accurately, e.g. psychiatric diagnoses, offence details, serious incidents of self-injury and violence.

See Fig. 3 for further information on which time point each procedure or measure is completed.

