Primary analysis of suicide ideation (BSSI) measured at 6 months (window 5–9 months) will use a linear mixed model with adjustment for baseline BSSI, stratification criteria and prognostic baseline covariates. The adjusted mean differences will be presented with 95% confidence intervals. BSSI is expected to be positively skewed and so the standard error and confidence interval for the treatment effect will be estimated by applying a bootstrap procedure [25] using the percentiles based on the results of 5000 replications (using the trial participant as the sampling unit). Primary analysis of suicidal behaviours (SB) measured within 6 months from randomisation will use a mixed model for count outcomes. The appropriate model with be chosen depending on the distribution of this variable. Analysis will adjust for baseline BS, stratification criteria and prognostic baseline covariates. The adjusted incident rate ratio will be presented with 95% confidence intervals. Due to the hierarchical ordering of these primary outcomes, no confirmatory claims can be made with regards to treatment benefit on SB unless it has first been demonstrated on BSSI. Secondary outcomes will be assessed using linear mixed models with similar adjustments. Analysis of primary and secondary outcome measures will be by intention to treat and will therefore include outcomes for all randomised participants in the group to which they were allocated, regardless of protocol adherence.

A therapeutic dose response model will be used to assess the effect of time engaged in therapy on treatment benefit. A complier average causal effect (CACE) model will be used to examine the treatment effect in those defined as ‘compliers’. Compliance will be defined from practitioner notes as a participant having started the ‘CBSP Phase’ of therapy. Treatment effect will be estimated within the subgroups defined by whether a participant has a history of suicide (Yes/No). As the study was not powered to investigate subgroup effects, this will be a purely exploratory analysis. All inferential analyses will adjust for stratification factors used in randomisation. Additionally, baseline outcome and prognostic variables will be adjusted for to improve power. Where outcome variables are skewed, bootstrapped confidence intervals will be presented. There will be no interim analysis of outcome data during the trial.

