All efforts will be made to obtain outcome data for randomised participants. This will include following up participants who transfer prisons or are released prior to their 6 month follow up assessment. Reasons for withdrawal of consent to follow up with be recorded and tabulated where participants are willing to provide a reason. The primary analysis will include all available data under a missing at random assumption. Sensitivity to missing data mechanisms will be assessed, and if required multiple imputation or inverse probability weighting used to account for missing outcomes.

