### Safety reporting

#### Adverse Events (AEs)

An adverse event (AE) reporting system will be used on the trial. Suicidal ideation, self-harm, harm to others and property will be routinely recorded and it is expected that these will occur for some participants. These will include, ideation alone with no behaviour (suicidal ideation or self-harm ideation), self-harm or suicidal behaviour (cutting self, biting and breaking the skin, severely scratching or running anything on the skin, using corrosive substances on the skin, sticking sharp objects into the skin, pulling out hair, burning with a cigarette lighter or match, scolding the skin, swallowing objects, choking or blocking airways, inserting objects into body cavities, overdosing with prescribed medication, overdosing with non-prescribed medication, taking illicit substances (not including medication), taking poisonous substances, inducing vomiting, over-eating, eating something that is known to cause an allergic reaction, food or fluid refusal, refusing medication, violence towards an inanimate object (e.g. a wall or door), ligaturing/hanging, drowning, severing body parts, electrocuting), events involving others (threats to harm others / violence, actual harm to others / violence). It should be noted that these may be Serious Adverse Events (SAEs) depending on the severity of injuries and outcomes of the behaviour. These events do not require further follow up unless there is evidence that these are research related but each event should be recorded from consent until 1 month after the final follow-up assessment is completed. Any untoward medical occurrence that is not included in the definition above will not be reported.

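### Suicidal behaviour, a co-primary count over 6 months, has self-report as its only named source: participants with no follow-up interview, including suicide deaths, have no count, and a month-5 interview cannot cover the period

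*Protocol article*

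**What the plan says.** The protocol article fixes the outcome and its period under Co-primary outcomes: "The second co-primary outcome is the number of occurrences of suicidal behaviour (SB) during the 6 months from randomisation". The next statement about data gives the source: "Instances of suicidal behaviour will be collected via self-report from participants", prompted by an adapted SASI interview. The Abstract (Methods) places assessment of both co-primary outcomes at baseline and the 6-month follow-up.

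The timing of that follow-up appears under End of trial, which refers to the last participant having "completed the 6 month (window of 5–9 months) follow up". Data analyses of the RCT repeats the window for the BSSI. For SB it says: "Primary analysis of suicidal behaviours (SB) measured within 6 months from randomisation will use a mixed model for count outcomes", with an adjusted incidence rate ratio as the effect measure. That section also says that intention to treat brings in the outcomes of everyone randomised. On missing data it says: "The primary analysis will include all available data under a missing at random assumption", followed by a promise to assess sensitivity to the missing-data mechanism, with multiple imputation or inverse probability weighting if needed.

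Three other sections collect information that bears on SB:

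- Demographic, clinical and criminological data allows access to clinical and prison records, with consent, for items such as "psychiatric diagnoses, offence details, serious incidents of self-injury and violence".
- Adverse Events (AEs) covers self-harm and suicidal behaviour, and says "each event should be recorded from consent until 1 month after the final follow-up assessment is completed".
- Serious Adverse Events (SAEs) sends fatal events to the oversight committees within seven days.

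No section links any of these to the SB count.

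**The concern.** The source and period of a co-primary outcome are protocol content, and here they do not fit together. If SB comes from the participant at one follow-up interview, three groups are not measured over the stated period: those never interviewed, those who have died, and those seen before month 6.

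The deaths matter most in principle. Suicide is the event that the trial aims to prevent, yet under the named source it yields a missing value and not a count. Missing at random is hard to defend for such a person. Standard multiple imputation or inverse weighting does not help, because imputing a count for a known suicide makes no sense. An analysis that leaves these people out favours whichever arm has more deaths.

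For the others lost, the BSSI gap may be unavoidable, because ideation over the last week has to be reported by the person. The SB gap is partly avoidable, because some events are already being recorded.

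**Working it through.** **1. How many have no interview-based count.** Inputs from Sample size calculation: analysis set 250, attrition up to 30%, total 360. The plan's own figure reproduces: 250 / (1 − 0.30) = 357.1, rounded up to 358, against 360 stated. At 30% loss, 360 × 0.30 = 108 have no interview-based SB count, and 252 do.

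**2. What the sources cover.**

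| Source | Content | Linked to SB in the article? |
|---|---|---|
| Follow-up interview | SB by self-report | Yes, the only one |
| Clinical and prison records, with consent | Serious self-injury | No |
| AE log | Self-harm and suicidal behaviour, within a wider list of events | No |
| SAE reports | Deaths | No |

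**3. The window.** An interview at month 5 covers 5/6 = 0.833 of a 6-month period. At a constant event rate the expected count is 16.7% short of the 6-month value for that participant. A later interview does not lengthen the outcome, which stays fixed at 6 months.

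The effect on the rate ratio depends on balance between arms. Suppose no exposure term were used, shares q_T (therapy) and q_C (control) were seen at month 5, and everyone else at 6 months or later. The rate ratio is then multiplied by (1 − q_T/6) / (1 − q_C/6):

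- equal shares: 1.00
- 50% versus 25%: 0.917 / 0.958 = 0.957
- 75% versus 25%: 0.875 / 0.958 = 0.913

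With an exposure term and a constant rate, the factor is 1.00 throughout.

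**4. Loss to follow-up.** The article gives no SB rate among those lost, so this is an illustration. Take an observed rate ratio of 0.40 (the 60% reduction in Sample size calculation). Assume that those lost have k times the SB rate of those seen, with the same k in both arms, and write m_T and m_C for the proportions lost. The rate ratio in everyone randomised is

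0.40 × [(1 − m_T) + k·m_T] / [(1 − m_C) + k·m_C].

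| Loss, therapy / control | k = 2 | k = 3 |
|---|---|---|
| 30% / 30% | 0.40 | 0.40 |
| 35% / 25% | 0.40 × 1.35/1.25 = 0.43 | 0.40 × 1.70/1.50 = 0.45 |
| 40% / 20% | 0.40 × 1.40/1.20 = 0.47 | 0.40 × 1.80/1.40 = 0.51 |
| 25% / 35% | 0.40 × 1.25/1.35 = 0.37 | 0.40 × 1.50/1.70 = 0.35 |

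Equal loss gives no bias. More loss in the therapy arm makes therapy look better than it is, and more loss in the control arm does the reverse.

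**5. Deaths.** The article gives no expected number. As a rough assumption, use the Background figures: 11 per 100,000 a year in the community, six times that in prison, and eight times again after previous suicidal behaviour. For half a year and 360 participants, 11 × 6 × 0.5 / 100,000 × 360 = 0.12 without the eightfold factor, and 0.12 × 8 = 0.95 with it. So about 0.1 to 1 death is expected on this basis. Multiplying the factors is crude, and the point does not rest on the number.

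**The case against.** The strongest reply is that much of this is silence, and the analysis plan is not shown. An exposure offset, window rules and the handling of deaths are often settled there. The article leaves even the form of the count model open, and an incidence rate ratio is compatible with an exposure term. It also plans missing-data sensitivity analyses, a comparison of those lost with those who stay (Elective discontinuation from the trial by individual participants), and follow-up after transfer or release. SB is ranked second, so no confirmatory claim on it is possible unless the BSSI succeeds first.

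Much of this stands, and it rules out several stronger readings that a reader might infer:

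- That suicide deaths are dropped. The article says nothing on how a death enters SB. A missing count follows from the named source, but exclusion is not a stated rule.
- That month-5 interviews are scored as if they covered 6 months. No section says so, and the absence of an offset from the article is no error.
- That using records would shrink the primary SB standard error in the ratio √(252/360) = 0.84. This would need records as informative as interviews for all 360. Records need consent, cover serious incidents only, and could not simply be pooled with self-report.
- That the AE log is a ready-made SB count. Its list is far wider than SB, and its end date is tied to a final assessment that some participants never attend.

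What the reply does not remove is what the article does fix: a 6-month period, a single named source, and an interview allowed before the period ends. The sensitivity methods it names do not deal sensibly with a known suicide death.

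Differential loss is also possible. Under Drop-out from trial intervention criteria, suicidal behaviour can prompt a review of whether therapy continues, which can happen only in the therapy arm. Those participants are still invited to follow-up, so this is a risk and not a prediction.

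**Conclusion.** The point holds in limited form. As written, SB is unmeasured for up to 30% of participants (about 108 of 360). These include anyone who dies by suicide, although the trial collects deaths and some self-injury data separately. The window does not fit a fixed 6-month count, since a month-5 interview covers about 5/6 of it.

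Bias in the rate ratio is conditional. In the model above, with the same excess rate among those lost in both arms, it is zero when loss and timing are balanced. With 2 to 3 times the SB rate among those lost and 35% versus 25% loss, an observed 0.40 corresponds to 0.43 to 0.45. These loss splits and rate multiples are assumptions, because the article gives neither.

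This is a correction to make before allocation codes are released. It falls short of a flaw that would invalidate the co-primary outcome.

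**What to change.** 1. Define SB as dated events within 6 months of randomisation. Where the interview falls earlier, use the observed time as exposure in the count model. Events after 6 months do not count.
2. State that a death by suicide within that period counts as an SB event, with exposure ending at death. State also whether that person's earlier non-fatal events, if known from other sources, are counted.
3. Pre-specify a supportive SB analysis in all randomised participants who consented to record access. Use prison and clinical records and those AE entries that meet the SB definition. Extract the data after the final assessment. Methods to protect against sources of bias already keep researchers from the full clinical notes until then, so blinding is preserved.

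The cost is some wording in the protocol and analysis plan, an event date on the eCRF, a record extraction and one additional analysis. The downside is that records capture less SB than interviews and depend on consent. The third analysis should therefore stay supportive and not be pooled with self-report, and no gain in precision should be claimed for the primary SB result.

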### Secondary suicide outcomes

Other important outcomes will also be assessed with all such secondary outcome established as highly correlated with suicide behaviour:The *Suicide Probability Scale* (SPS: [16]) will be used to assess future suicide potential. The 36-item SPS was developed to measure four dimensions of suicide experience: hopelessness, suicide ideation, negative self-evaluation, and hostility. In a sample of mental health inpatients, the SPS demonstrated high internal reliability with a Cronbach’s alpha of 0.92 (Bisconer and Gross, 2007).The *Brief Suicide Cognitions Scale* (B-SCS; [77]) provides a measure of thoughts, perceptions, and beliefs that are commonly experienced by people who have attempted suicide. A Cronbach’s alpha coefficient of 0.91 has been reported for psychiatric inpatients indicating good internal consistency, coupled with a test–retest reliability coefficient of 0.84 [77].

